## Method/design

### Study setting

The proposed Randomized Controlled Trial is a large-scale trial designed to assess the impact of an innovative navigation program denoted CAPRI, that is based on two Nurse Navigators and a web portal and ensures coordination between community and hospital as well as between patients and navigators, within the context of routine delivery of oral anticancer therapies. The broad research aim is to assess (a) the program’s impact on oral therapeutic delivery for patients with metastatic cancer treated with oral chemotherapy and/or targeted therapy, and (b) CAPRI’s effectiveness in terms of the treatment’s toxic side effects, tumor response, Progression Free Survival, Overall Survival, patient quality of life and patient experience, and (c) the economic evaluation of the CAPRI program.

The study will evaluate the CAPRI’s efficacy in comparison with usual care. The RCT will randomize 1,000 individuals fulfilling inclusion criteria into either the CAPRI group or the control group, for a 6-month period (Fig. 1). Participant outcomes could be assessed at baseline (T0) and each month of intervention, excepted for quality of life (T1 – T6) and patient experience (T6). Control group participants will be offered the intervention when the CAPRI program ends for the intervention group.

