#### Secondary endpoints

Secondary endpoints will be patient adherence to oral anticancer therapy, quality of life (functional scales, symptom scales, global health status and quality-of-life scales), patient experience, tumor response, Progression Free Survival (PFS), Overall Survival (OS) and toxic side effects of the therapy (severity and quantity). We expect that patients in the intervention arm, by comparison with controls, will demonstrate significantly greater improvements in secondary outcomes measures. Demographic, socio-economic and clinical variables will be assessed and considered in order to adjust the study results. These adjustment factors could be used to make stratified group comparisons.

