#### Instruments of measurement

Outcomes will be assessed by a Clinical Research Associate (ARC) at baseline, and each month until the end of the program (after 6 months), excepted for patient quality of life (at baseline, after 3 months and at the end of the program) and for patient experience (at the end of the program). Instruments used to collect data from participants, including primary and secondary outcomes, are listed in Table 2.

**Table 2 Tab2:** Variables and Instruments used for data collection

Measurement tools ARC administered (face to face interview)		Time point			
		At baseline	Each month	After 3 month	After 6 months
Demographics and general medical history	Age, gender, comorbidities	*			
Socioeconomic status	Education, income, employment, family characteristics	*			
Diagnosis	Cancer type, stage	*			
Autonomy	OMS score [55]	*	*	*	*
Treatment Delivery	RDI ratio [30] Morisky questionnaire [56] MEMs (only for targeted therapy) [57]		*	*	
Toxic effects	NCI-CTC-AE (CTCAE v4.0)		*	*	
Overall Survival	OS		*		
Progression Free Survival	PFS		*		
Tumor response	RECIST [58]		*		
Quality of life	EORT QLQ-C30 [59]	*		*	
Patient experience Satisfaction	PACIC [60]				*

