### Data analysis

Appropriate descriptive statistics will allow presentation and comparison of sample characteristics at baseline, and at each evaluation time point. The primary analyses will utilize a between-group design (CAPRI versus control groups) at six time points (each month)). Significant change in treatment delivery will be measured on the RDI ratio, calculated with the Morisky score and/or the Medication Event Monitoring System (MEMs) results. If distribution is normal, a student *t*-test will be used to compare RDI means, as well as secondary outcomes designed as continuous variables. If not, a Mann–Whitney test will be used. Chi2 or Fisher’s test will be used to compare secondary outcomes designed as binary variables. Baseline data will be examined to analyze probability of attrition bias.

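### The tests fixed for continuous secondary outcomes take no covariate, so QLQ-C30 comparisons lose precision that the collected baseline score could supply

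*Protocol article*

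**What the plan says.** The Secondary endpoints section of the protocol article lists "quality of life (functional scales, symptom scales, global health status and quality-of-life scales" among the secondary outcomes. It expects that intervention patients "will demonstrate significantly greater improvements in secondary outcomes measures".

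Instruments of measurement says that outcomes are assessed monthly, "excepted for patient quality of life (at baseline, after 3 months and at the end of the program". Table 2 names the QLQ-C30 and marks it at baseline.

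Data analysis fixes the test. A Student t-test, if the distribution is normal, "will be used to compare RDI means, as well as secondary outcomes designed as continuous variables". The fallback is equally definite: "If not, a Mann–Whitney test will be used". The quantity compared (score at follow-up, or change from baseline) is not stated. Apart from describing and comparing sample characteristics, the section uses baseline data only to look at attrition.

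On adjustment, Secondary endpoints says: "Demographic, socio-economic and clinical variables will be assessed and considered in order to adjust the study results". It adds: "These adjustment factors could be used to make stratified group comparisons". It names neither the baseline QLQ-C30 score nor a model.

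**The concern.** A baseline measurement of the same scale is usually the strongest available predictor of the follow-up score. The trial pays for that measurement, but the tests it names cannot take it as a covariate. Two consequences follow.

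- **Precision.** Whichever quantity the t-test is applied to, the standard error is larger than that of a baseline-adjusted comparison.
- **Open choice of quantity.** Follow-up score and change score have different variances. The same data can cross the 5% line under one and not the other, and the normality check that selects between t-test and Mann–Whitney could also come out differently.

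The loss falls on a patient-reported outcome that will help to judge whether the navigation program benefits patients.

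**Working it through.** **Plan's own figure.** Sample size calculation gives 393 per group for Relative Dose Intensity: difference 5, SD 25, α = 0.05, power 80%. Two-sided:

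n = 2 × (1.960 + 0.842)² × 25² / 5² = 2 × 7.849 × 25 = 392.4, rounded up to 393.

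The figure reproduces. The standardized effect is 5/25 = 0.20 SD. No corresponding figure is given for quality of life.

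**Assumptions for quality of life** (none is in the document):
- effect 0.20 SD, borrowed from the Relative Dose Intensity design for illustration;
- 393 analysed per group, the plan's number before its attrition allowance;
- equal SD at baseline and follow-up;
- baseline to follow-up correlation r = 0.3, 0.5 or 0.7.

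**Variance factors** relative to a t-test on the follow-up score:
- follow-up score: 1
- change score: 1 + 1 − 2r = 2(1 − r)
- baseline as covariate (ANCOVA): 1 − r²

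The change-score factor exceeds the ANCOVA factor by 2(1 − r) − (1 − r²) = (1 − r)², which is positive for any r below 1. The follow-up factor exceeds it by r², which is positive for any nonzero r. So the ranking does not depend on the assumed r; only the size of the gain does.

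**Standard errors and power.** SE = √(2 × factor / 393) in SD units. Power is from the normal approximation, Φ(0.20/SE − 1.96).

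| Analysis | r | Factor | SE | Power |
|---|---|---|---|---|
| Follow-up score | any | 1.00 | 0.0713 | 80.1% |
| Change score | 0.3 | 1.40 | 0.0844 | 65.9% |
| Change score | 0.5 | 1.00 | 0.0713 | 80.1% |
| Change score | 0.7 | 0.60 | 0.0553 | 95.1% |
| ANCOVA | 0.3 | 0.91 | 0.0681 | 83.6% |
| ANCOVA | 0.5 | 0.75 | 0.0618 | 89.9% |
| ANCOVA | 0.7 | 0.51 | 0.0509 | 97.5% |

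The number per group for 80% power under ANCOVA is 392.4 × factor, rounded up: 358, 295 and 201 at r = 0.3, 0.5 and 0.7, against 393 for the follow-up score. The difference detectable with 80% power at 393 per group falls from 0.200 SD to 0.191, 0.173 and 0.143 SD.

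These figures concern the t-test. The Mann–Whitney fallback takes no covariate either, but its power is not computed here.

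**The case against.** **The article is condensed.** The choice of covariates for a secondary scale often sits in the full protocol or analysis plan, neither of which is shown. That would answer a complaint about silence. But Data analysis is not silent: it commits to two named tests, and a later plan using a baseline-adjusted model would depart from them.

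**Adjustment is foreseen.** This is true in general terms. But the sentence only says that variables will be considered, the stratified comparisons are optional, and the baseline QLQ-C30 score is not mentioned.

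**A reader might infer a contradiction** between the improvement wording in Secondary endpoints and the two-sample tests in Data analysis. The text does not support this. The same sentence covers overall survival, progression-free survival and patient experience. The first two have no change from baseline, and the third is measured only at the end of the program. The wording therefore reads as better results than controls and does not define a change score.

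**A reader might also infer that the baseline score is left out of the test.** That is not established. A t-test on change would use it and fit both sections, though less efficiently than a covariate.

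**The size is assumed.** This stands. At r = 0.3 the gain over follow-up scores is only about 3.5 percentage points of power.

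**Baseline is collected after randomization.** This also stands. Participant recruitment procedure places it there and does not say whether patients already know their arm. If they do, the score could be influenced by allocation, and adjusting for it could introduce bias that a follow-up-only comparison avoids.

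**Conclusion.** The point holds as an efficiency matter on a secondary endpoint. The named tests are valid under randomization: chance baseline imbalance is already reflected in the standard error, so this is not bias. The Relative Dose Intensity sample size of 393 per group is unaffected.

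That baseline adjustment is more precise than a t-test on either quantity follows for any correlation strictly between 0 and 1, with equal SDs and a baseline unaffected by allocation. The amount is conditional. Under the stated assumptions, adjustment raises power from 80% to between 84% and 97.5% relative to follow-up scores. At r = 0.3, change scores would do worse than ignoring baseline (66% against 80%). At r = 0.5 the gain over either unadjusted version equals 1/0.75 = 1.33 times the sample size. Leaving the compared quantity unstated adds an avoidable choice at analysis.

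**What to change.** In Data analysis, replace the t-test or Mann–Whitney test for the QLQ-C30 scales by ANCOVA or a repeated-measures linear model on the month-3 and month-6 scores. Use arm as factor and that scale's own baseline score as covariate, and report the adjusted mean difference at month 6 with its confidence interval. State in Secondary endpoints that, for quality of life, improvement means this difference.

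Record for each patient whether the baseline score was obtained before the allocation was known. Report the unadjusted comparison of follow-up scores as a sensitivity analysis.

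While editing, reconcile the quality-of-life timing in Study setting, "excepted for quality of life (T1 – T6) and patient experience (T6", with the baseline, 3-month and end-of-program schedule in Instruments of measurement.

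The cost is wording, one standard model and one timing item. No extra patients or questionnaires are needed. Recruitment began in October 2016, so for patients already enrolled the timing may have to be taken from existing dates, and where it cannot be established the sensitivity analysis carries more weight.

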### Sample size calculation

Given previous research showing Relative Dose Intensity (RDI) varying from 60% to 95% for oral therapeutics in cancer care, considering a Relative Dose Intensity lower than 85% as a signal for reduced survivorship, and considering that a difference of 6% to 20% was found between different treatment options or between different cancer types, we expect a sizeable effect of the CAPRI program on patient RDI (5% difference with the control group) [29–32]. Therefore, 393 individuals per group will be sufficient to detect a difference in RDI between the CAPRI program and usual care, assuming significance is set at 5% (α = 0.05) power at 80% and a standard deviation of 25% for the distribution of mean change. We will include an additional 27% (*N* = 107 per group) to allow for attrition.

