### Randomization procedure

In accordance with CONSORT guidelines [33, 34], randomization will occur once participants have completed their consent form. Given the potential difference in adherence and socioeconomic status among the different cancer types [35, 36], stratified randomization might be used in order to minimize these differences between and within groups. This randomization will be done via computer software and completed by an independent researcher (Gustave Roussy randomization department). A randomization number will be allocated to each participant, and results of the randomization will be sent to both the therapist and the nurse navigators. Participants included in the intervention arm will be given immediate access to the CAPRI program, including access to their personalized online portal.

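### A normality check on the trial's own RDI data chooses the primary test, and the likely choice, Mann–Whitney, is not the comparison of means for which the trial was sized

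*Protocol article*

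**What the plan says.** **Test.** Under Data analysis, a t-"test will be used to compare RDI means, as well as secondary outcomes designed as continuous variables" applies if the distribution is normal. "If not, a Mann–Whitney test will be used" otherwise. The article names no normality test or threshold.

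**Sizing.** Under Sample size calculation: "we expect a sizeable effect of the CAPRI program on patient RDI (5% difference with the control group"), "assuming significance is set at 5% (α = 0.05) power at 80"%, and "a standard deviation of 25% for the distribution of mean change". This gives 393 per group before attrition. The same paragraph puts earlier RDI values between 60% and 95% and notes that "a difference of 6% to 20% was found between different treatment options or between different cancer types".

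**Endpoint.** Under Primary endpoint, RDI is the delivered dose divided by the prescribed dose intensity. No upper limit is stated.

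**Cancer type.** Under Randomization procedure, "stratified randomization might be used in order to minimize these differences between and within groups". Under Secondary endpoints, patient background and clinical factors are to be considered for adjusting the results, followed by: "These adjustment factors could be used to make stratified group comparisons". Table 2 lists cancer type as a baseline item. The test sentence in Data analysis contains no covariate.

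**The concern.** The t-test and Mann–Whitney answer different questions. The t-test concerns the difference in mean RDI. Mann–Whitney concerns whether a patient in one arm tends to rank above a patient in the other. Under the stated rule, the trial learns which question is primary only after looking at the shape of its outcome.

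The sample size rests on the first question. If the check leads to the second, the trial may end with a p-value that says nothing direct about the 5-point hypothesis, no planned estimate of that difference, and a power that nobody has calculated.

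A lesser issue is that the plan itself expects sizeable RDI differences between cancer types or treatments, yet does not tie any adjustment to the primary comparison.

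**Working it through.** **1. Reproduce the sample size.** Inputs from Sample size calculation: difference 5, SD 25, α = 0.05 (taken as two-sided), power 80%.

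n per group = 2 × (1.960 + 0.842)² × 25² / 5² = 392.4, rounded up to 393.

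This matches exactly; a one-sided test would need 310. The figure is therefore a two-sided comparison of means, with 25 acting as the between-patient SD. Power at 393 per group: Φ(5 / (25 × √(2/393)) − 1.960) = 80.1%.

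**2. Could RDI be normal with SD 25?** The share of a normal curve above 100% is 1 − Φ((100 − mean)/25):

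| Assumed mean RDI | Share above 100% |
|---|---|
| 60 | 5% |
| 80 | 21% |
| 85 | 27% |
| 95 | 42% |

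The means 60 and 95 are the ends of the range that the plan cites; 80 and 85 lie between them. If delivered dose seldom exceeds prescribed dose, these shares cannot occur and the distribution must be skewed or piled up near the top. Beta distributions on 0–100% with SD 25 and control means of 60 to 85 failed a Shapiro–Wilk test (chosen here, since the plan names none) in 100% of simulated trials at 393 per arm. Under that assumption the rule selects Mann–Whitney.

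**3. Power of each test for the same 5-point mean gain.** Simulation with 393 per arm and 3,000 replicates. All shapes are assumptions.

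| Assumed RDI shape | t-test | Mann–Whitney |
|---|---|---|
| Beta, SD 25, mean 60 to 65 | 81% | 85% |
| Beta, SD 25, mean 70 to 75 | 80% | 94.5% |
| Beta, SD 25, mean 80 to 85 | 80% | about 100% |
| 40% at full dose; gain only in the low tail | 68% | 26% |
| Same control arm; gain concentrated at full dose | 58% | 99.7% |

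In the last two rows the control arm has 40% at 100%, 25% uniform on 0–50% and the rest uniform on 60–100%. The gain comes either from cutting the low share to 15.9% or from raising the full-dose share to 65%. SDs there are 27 to 33, which is why the t-test falls below 80%.

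**4. Type I error.** The two-stage rule gave 4.8% to 5.6% in the beta null cases. Welch's t-test on beta data gave 5.1%, so a comparison of means is valid at this size without normality.

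**5. Gain from adjusting for cancer type.** The documents give no R². Assume two equal groups differing by d points: R² = (d/2)² / 625.

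- d = 6: R² = 9/625 = 0.0144; residual SD 25 × √0.9856 = 24.8; power 80.6% (80.5% with the t distribution).
- d = 20: R² = 100/625 = 0.16; residual SD 25 × √0.84 = 22.9; power 86.4% (86.3% with the t distribution).

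For assumed R² of 0.05, 0.10, 0.20 and 0.30, power is 82.0%, 84.0%, 88.0% and 91.8%.

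**The case against.** **The switch may help rather than harm.** Under beta-shaped RDI with the plan's SD, Mann–Whitney beats the t-test by about 4 to 20 power points. This stands. A reader might infer from the low-tail scenario (26% against 68%) that the rule costs power. The documents do not support that, because they give no RDI distribution and other shapes reverse the result.

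**Validity is not at risk.** This also stands. A reader might suspect that choosing the test from the data inflates type I error, but the simulated rate stayed near 5%.

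**The ceiling is assumed.** The article states no cap at 100%, and it attaches the SD of 25 to a change rather than to individual RDI. Failure of normality is therefore a strong inference, not a fact taken from the plan.

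**The plan does not ignore cancer type.** A reader might conclude that it does from the test sentence alone. Secondary endpoints foresees adjustment for clinical factors, cancer type is collected at baseline, and stratified randomization is considered. The optional wording there concerns stratified comparisons, not adjustment as such. What remains is that none of this is tied to the primary test.

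**Covariates and model form belong in the SAP.** True in general, and the SAP is not shown, so their absence is not a defect. The test-selection rule is different: the article states it outright.

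**Conclusion.** The concern holds in a limited form. The protocol lets a normality check choose the primary test, while 393 per group is sized for a 5-point difference in means. If RDI is bounded at or near 100%, Mann–Whitney is the probable primary test. It would leave the powered hypothesis untested and unestimated, with power anywhere from about 26% to nearly 100% over the shapes examined.

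The harm is a target of inference that depends on the data and a power that is unknown. Neither inflated type I error nor a consistent loss of power follows. The missing link between adjustment and the primary test is a secondary matter worth roughly 0.5 to 6 power points in the two-group illustration. The conclusion rests on the assumed ceiling, on reading the SD of 25 as between-patient, and on the assumed shapes and R². It should be corrected, but it does not invalidate the trial.

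**What to change.** Delete the normality-dependent choice for RDI. Name one primary analysis before unblinding: the between-arm difference in mean RDI with its 95% CI, from a linear model with robust standard errors, adjusted for baseline cancer type and for any stratification factor actually used. Keep Mann–Whitney as a labelled sensitivity analysis. How the six monthly RDI values form the analysed outcome is a separate question that this change does not settle.

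The cost is wording only: cancer type is already collected at baseline and the sample size stays as it is. The downside is that for some RDI shapes, including the beta cases above, a rank test would have had more power.

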### Trial status

The trial began in October 2016 with recruitment to the study. Nurse Navigator training is complete and the web portal’s testing phase is over. It is anticipated that full post-intervention data will be completed by September 2018. Clinical trial number is posted on www.clinicaltrials.gov/.

## Discussion

The proposed study aims to provide a rigorous assessment of the impact of a program - based on Nurse Navigation and Health Information Technology - on oral therapeutic delivery for patients with metastatic cancer.

### Study advantages and disadvantages

Assessing delivery of oral anticancer therapy through measurement of both medication adherence and Relative Dose Intensity needs rigorous methods. Based on the results of previous studies [6], we decided to use the RDI measure using a self-reported questionnaire (Morisky), combined with a MEMs for patients receiving targeted therapy. This two-fold strategy should enable us to avoid the risk of adherence overestimation for psychological reasons (shame, guilt) [4, 39]. It has been presented as the most relevant strategy for measuring medication adherence [40] when the use of objective methods (such as blood sampling) is not possible.

The implementation of a medico-economic evaluation nested within our study is innovative; to our knowledge, evaluations of navigation programs in oncology targeting the treatment phase have been scarce [41]. Economic evaluations are encouraged by experts in this field [42] since they allow us to formulate policy and resource allocation implications, such as the development of financial incentives to improve care coordination. Improving patient adherence to oral anticancer therapy and improving their Relative Dose Intensity via a navigation program combined with Health Information Technology - is challenging for the organization of healthcare. Indeed, improved adherence to oral treatment would probably favor community care for patients with cancer, which would in turn imply reduced unplanned activity for hospitals and increased activity for community cancer care. Changes in patient follow-up will generate a need to better inform (train) community care professionals (which could be supported by a navigation program offering a web portal for professionals, as CAPRI does) [43] and adaptation of the payment system to this new care organization, which requires increased coordination between primary and secondary care [44].

The fact that it is designed as a randomized controlled trial is another of our study’s assets. Few high-quality studies provide an evaluation of coordination programs in cancer care, especially combining both Nurse Navigation and Health Information Technology [43–47]. RCT has been considered the gold standard for evaluating organizational interventions [48]. Portela showed that RCTs are relevant for interventions that are expected to be widespread, because of their validity and their evidence-based results [45]. However, this type of trial is based on the biomedical model that assumes a linear causation, which may be irrelevant when considering organizational interventions [45, 48]. Indeed, the effects of such interventions could be attributed to the influence of psychological or social confounders, especially in barely-controlled environments. Nielsen suggested that RCT for organizational interventions should be complemented by another type of evaluation, capable of detailing the implementation processes of an intervention in addition to its ‘direct’ effects [37, 49].

Combining RCT with process evaluation, as we will do in our study, may lead to improved understanding of the impact of such interventions, since it may bring knowledge of the enabling and impeding factors influencing their implementation. [44, 49–51]. It could explain how, why and when organizational interventions generate improvement, taking implementation duration into account [52–54] more effectively than RCTs.

